## Abstract

**Introduction:** Parkinson's disease (PD) is a common neurodegenerative disease that seriously impairs patients' quality of life, and increases the burden of patients and caregivers. Both drugs and exercise can alleviate its motor and non-motor symptoms, improving the quality of life for PD patients. Telehealth, an increasingly popular tool, makes rehabilitation accessible at home, overcoming the inconvenience of traffic and scheduling. Care-PD is a phone application designed for rehabilitation training, which provides Tai Chi and stretching exercises through tutorial videos as well as an online evaluation system. In this protocol, we will explore the efficacy of Tai Chi and stretching exercises as a PD rehabilitation therapy based on the smartphone application Care-PD.

**Methods and Analysis:** A double-blind, parallel randomized controlled trial will be conducted in this study. The recruitment, intervention, and evaluation processes will be implemented through the Care-PD application. Persons with PD will fill out questionnaires on Activities of Daily Living (ADL), upload the latest case report, and sign the informed consent form in the application. Afterward, doctors and researchers will screen and enroll 180 participants who will be randomly (1:1:1) assigned to Tai Chi group, stretching exercises group, or control group. The subjects will participate in a 1-h exercise session three times per week for 12 weeks, ending with another 4 weeks of follow-up study. Each exercise session includes 10 min of warm-up, 45 min of exercise, and 5 min of cool-down. The primary outcomes are Motor Aspects of Experiences of Daily Living and the 39-item Parkinson's disease Questionnaire. The secondary outcomes include the 9-item Wearing-Off Questionnaire, the Freezing of Gait Questionnaire, the Caregiver Strain Index, Non-motor Experiences of Daily Living, ADL, and Morse Fall Scale. All assessments will be performed at baseline, week 12 and 16.

**Discussion:** Care-PD integrates subject recruitment, intervention, and evaluation, providing a new perspective on clinical rehabilitation for persons with PD. This study will evaluate the efficacy of Tai Chi and stretching exercises on patients' quality of life and disease progression based on a smartphone application. We aim to provide a new rehabilitation training platform for persons with PD.

**Ethics and Dissemination:** This study was approved by the Scientific Research Ethics Committee (102772020RT132) of Shanghai University of Sport. Data collection begins after the approval of the ethics committee. The participants must sign an informed consent form before enrollment. The results will be published in relevant journals, seminars, and be disseminated among rehabilitation practitioners and patients with PD.

**Clinical Trial Registration:** Chinese Clinical Trial Registry, identifier [ChiCTR2100042096]. Registered on January 13, 2021.

## Introduction

Parkinson's disease (PD) is a complex and evolving neurodegenerative disease (1–3). The causes of PD have not yet been fully elucidated. The latest research indicates that gene mutation, environmental exposure, and the presence of Lewy bodies may cause PD (4, 5). The incidence of PD is low before the age of 50 but increases rapidly with age, peaking at approximately the age of 80. In most studies, the incidence ratio of males to females is about 1.3–2.0 (6).

Currently, PD affects the daily lives of nearly 6.1 million people worldwide (4). In China, the incidence of PD is rising sharply as population aging aggravates (7). It is estimated that the number of PD patients will increase to 4.94 million by 2030, accounting for nearly half of the cases worldwide. This may impose a considerable burden on the nation's economy and medical system (8). The symptoms and signs of PD can be categorized as motor and non-motor symptoms. Motor symptoms include tremor, stiffness, slow movement, postural instability (1), and freezing of gait (FOG). Non-motor symptoms include cognitive impairment, pain, fatigue, mental symptoms (depression, anxiety), and sleep disorders (9, 10). PD not only severely affects patients' quality of life (QoL) but also increases caregivers' psychological pressure and physical burden (11).

The standard treatments for PD are pharmacologic (levodopa) or non-pharmacologic (exercise, speech therapies) (12). Pharmacologic therapy helps alleviate motor symptoms. However, long-term pharmacologic therapy is accompanied by motor complications, such as dyskinesia and wearing-off phenomena (13). In severe cases, the progression of PD can impair patients' cognitive function (14). Therefore, finding a safer approach is of urgent necessity.

Studies have shown that exercise not only improves cardiopulmonary function, immune function (15), and psychological states but also prevents depression, PD, and Alzheimer's disease (16–18). However, most types of exercise are difficult to popularize among the elderly, especially those with PD.

Tai Chi, a popular exercise among the elderly, is slow-paced and fluent (19). In recent years, the positive effect of Tai Chi on PD symptoms has aroused widespread interest. Hackney et al. presented that Tai Chi improved the balance and mobility of patients with PD (20). Li et al. (21) also found that Tai Chi effectively reduced balance disorders, improved functional capacity, and reduced the incidence of falls in patients with PD. Recently, research indicates that Tai Chi also has a positive effect on cognitive function, sleep quality, and mental health (21–24). However, Shinichi Amano et al. presented that class-based Tai Chi exerted no significant effect on gait or disability rates. According to a systemic review and meta-analysis of seven randomized controlled trials, Tai Chi effectively reduced the incidence of falls (22). In contrast, another meta-analysis suggested no conclusive evidence supporting that Tai Chi can significantly improve the gait velocity and gait endurance (25, 26). Thus, the efficacy of Tai Chi on PD remains to be determined and may be related to the compliance of patients (27).

Tai Chi is typically practiced in groups under the guidance of a coach with rich experience. Unfortunately, the COVID-19 epidemic prevented persons with PD from participating in outdoor activities, possibly worsening their motor and non-motor symptoms (28). Therefore, it is urgent to devise an innovative rehabilitation method accessible to patients at home.

Telehealth based on smartphone applications (app) has developed rapidly, becoming increasingly popular during the COVID-19 pandemic (29). Smartphone apps do not require face-to-face communication between doctors and patients, thereby maintaining social distancing and preventing the spread of the virus (30). Telehealth makes rehabilitation accessible at home, overcoming the inconvenience of traffic and scheduling, and also alleviates the financial burden for patients (31, 32). Telehealth provides a new perspective on home rehabilitation for patients with PD.

Until now, there have been few studies dedicated to home rehabilitation training based on smartphone apps for patients with PD. The Merrill R Landers team created the 9zest app, providing various types of exercise videos, ranging from aerobic exercise, resistance exercise, to yoga and balance training. Their study confirmed the feasibility and safety of app-based exercise (33). However, it lacked an evaluation program that tracks the efficacy of patients' exercise in real time. To overcome the limitations mentioned above, our team developed the Care-PD app, providing home rehabilitation training for patients with PD. Care-PD incorporates Tai Chi, stretching exercises videos, as well as the Self-Assessment module. However, randomized controlled trials on Tai Chi and stretching exercises based on the app are yet to be conducted. This study will conduct recruitment of persons with PD, exercise intervention, and outcome evaluation solely based on the Care-PD app (34).

This study aims to determine the practicability of recruiting subjects, conducting exercise intervention, and evaluating outcomes using a smartphone app only. Additionally, we will explore the effect of Tai Chi and stretching exercises on PD progression. This is the first online randomized controlled trial entirely based on a smartphone app in China. We hypothesize that compared to stretching exercises, Tai Chi is more effective in improving QoL and disease progression.

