### Participants

We will conduct online recruitment (e.g., WeChat) and post advertisements in communities and hospitals to recruit more participants. The researchers in charge of recruitment will remotely guide participants through the registration process. The subjects with PD interested in our research will sign up for the phone app.

Before enrollment, participants will be comprehensively evaluated based on the following items: (1) diagnosis certificate or recent medical records uploaded in Care-PD (Supplementary Figure 1A), (2) Activities of Daily Living (ADL) index scoring (35, 36), and (3) remote video conference evaluation conducted by professional neurologists. The video conference utilizes two cameras (the primary camera and the secondary camera) to remotely monitor the subjects' performance.

We plan to recruit 180 participants who will be divided into three groups using a 1:1:1 randomization formula: Tai Chi group, stretching exercises group, and control group. Every eligible subject will sign the informed consent form in the app (Supplementary Figure 1B).

The inclusion criteria for subjects with PD are:

(1) Diagnosis of idiopathic PD,(2) Age of 40 to 75 years with the ratio of males to females ~1–1,(3) Currently receiving pharmacologic treatment (levodopa) under stable conditions,(4) Scoring over 55 in ADL index,(5) Willingness to cooperate with treatment and sign the informed consent form.

The exclusion criteria are:

(1) Diagnosis of typical PD,(2) Inability to stand for 45 min or complete exercise training,(3) High risk of falls in the next 6 months indicated by Morse Fall Scale (MFS) (37),(4) Severe cognitive or mental disorders verified through remote video conference with the help of caregivers,(5) Inability to use a smartphone or lack of assistance from family members or caregivers to do so.

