### Intervention

All subjects will take medicine according to prescriptions and record the use of medicine in the Medication Recording module (37). Exercise videos of Tai Chi and stretching exercises will be uploaded to the Exploratory Research module in advance. Each Tai Chi and stretching exercises session consists of 10 min of warm-up, 45 min of exercise, and 5 min of cool-down. The program will last for 12 weeks, with each week containing three sessions of 1-h long exercises, followed by 4 weeks of follow-up without intervention. To ensure safety, subjects will be asked to clear up the surroundings in advance with the assistance of caregivers.

In addition, WeChat and Tencent Meeting will be used for communicating with the participants. Before each intervention, Care-PD will send a notification as well as a text message to remind the participant to exercise according to schedule. During the intervention, a video conference will be initiated that the subjects then join with the camera on. The entire process of the exercise intervention will be supervised and recorded. The researchers will inform subjects on the techniques of exercise, safety precautions, and emergency measures in case of adverse events. At the end of the intervention, the researchers will remind the subjects to log in and inquire about changes in their physical and psychological conditions. The specific plan of intervention is shown in Figure 3. The detailed moves of Tai Chi and stretching exercises are presented in Table 2.

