### Adherence Promotion

Participant adherence is measured by the rate of recruitment and retention, online time, and other adherence performance. Coaches and doctors are responsible for supervising and managing the participants:

(1) Before each exercise, the attendance rate will be counted.(2) During the exercise, log-in time in the video conference and Care-PD app will be recorded, respectively. Moreover, coaches will supervise the exercise through video conference which will be recorded and reviewed subsequently.(3) Before and after the intervention, the time spent on filling online questionnaires will also be recorded.

In addition, the subjects will receive verbal encouragement and humanistic care. We plan to reward participants for following instructions to improve their adherence to the program. Immediate results from the assessment module in the application will also create a positive feedback loop that stimulates participant adherence.

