During the COVID-19 pandemic, face-to-face assessment is risky and inconvenient. Therefore, it is necessary to build an online evaluation platform for home rehabilitation exercises. Care-PD is a home rehabilitation app, providing Tai Chi and stretching exercises videos created by professional coaches and neurologists. Patients can not only exercise under the guidance of tutorial videos but also track disease progression in the app. The most significant difference between our study and the protocol of Gao et al. (34) is that our study is entirely based on the mobile app, which integrates subject recruitment, exercise intervention, and outcome evaluation. Gao et al. introduced the platform of Care-PD in management and rehabilitation for persons with PD. Despite the lack of significant difference between Tai Chi group and the control group, they demonstrated that after 8 weeks of rehabilitation using Care-PD for Tai Chi and medicine management, both the motor and non-motor symptoms of participants improved. Thus, the Care-PD platform is a viable option for home rehabilitation.

This study will explore the effect of Tai Chi and stretching exercises on QoL, motor and non-motor symptoms for persons with PD utilizing the Care-PD app. In the future, we plan to further promote and popularize the Care-PD app among persons with PD. However, there still exists certain limits. First, the majority of PD patients are between 60 and 80 years old and cannot operate mobile phones readily. Second, it is difficult to ensure the consistency of exercise intensity and duration for every participant as exercise intervention is conducted remotely. Last, outcomes can only be assessed through online questionnaires in the app. Physical examinations that require face-to-face contact, such as the 6-Min Walk Test, Timed Up and Go test, Limits of Stability, and Functional Reach Test, cannot be performed.

Moreover, the subjects need to maintain their habitual lifestyles, physical activity, and avoid participating in other exercise programs.

In conclusion, we hope that Care-PD and its exercise and assessment features can reach more PD patients in need of home rehabilitation, ultimately improving their QoL as well as motor and non-motor symptoms. Care-PD will serve as a rehabilitation platform assisting PD patients and caregivers, as well as guides and other materials for the reference of neurologists.

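### The first aim claims app-only practicability, but outreach, screening and training also rest on other channels and live staff, so only the package as delivered can be judged

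*Protocol article*

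**What the plan says.** The Introduction opens its statement of aims with "This study aims to determine the practicability of recruiting subjects, conducting exercise intervention, and evaluating outcomes using a smartphone app only". Just before that, it makes clear which app is meant: "This study will conduct recruitment of persons with PD, exercise intervention, and outcome evaluation solely based on the Care-PD app (34"). It goes on to call the trial the first of its kind in China to be run entirely through a smartphone app. The Discussion repeats that "our study is entirely based on the mobile app" and presents this as the main difference from a related earlier protocol.

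The methods sections describe more than the app:

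- **Outreach (Participants):** "We will conduct online recruitment (e.g., WeChat) and post advertisements in communities and hospitals to recruit more participants".
- **Registration (Participants; Recruitment):** researchers guide people through it remotely, and administrators help subjects or caregivers install the app and register.
- **Screening (Participants):** besides uploaded records and the ADL score, neurologists evaluate each candidate by video conference, using two cameras.
- **Training (Intervention):** "WeChat and Tencent Meeting will be used for communicating with the participants", and "During the intervention, a video conference will be initiated that the subjects then join with the camera on". The whole of the exercise intervention is to be supervised and recorded. The Tai Chi Group section adds a remote specialist, and Adherence Promotion adds coaches who supervise by video.
- **Measures (Adherence Promotion):** "Participant adherence is measured by the rate of recruitment and retention, online time, and other adherence performance". Attendance, log-in time and time spent on questionnaires are also recorded there. The eight named outcomes are all clinical or caregiver scales.

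**The concern.** The first aim attributes to the trial a property that its conduct does not have. If recruitment and attendance go well, the natural reading of the aim is that a smartphone app alone was enough to find, enrol and train people with Parkinson's disease. Yet participants will have been reached partly through other media, helped by staff to get started, seen by a neurologist on video, and coached live while exercising. Any of these could account for good recruitment or attendance, and nothing in the design separates them from the app.

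This matters beyond wording because the Discussion foresees promoting the app more widely among people with the disease. A service that is the app alone and a service that includes a live coach three times a week differ in cost and in likely uptake. The aim also has no outcome attached: the data that bear on it are collected, but only as measures of adherence.

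**Working it through.** No formula in the protocol is at issue. The check sets the aim beside the conduct, one process at a time, and then counts how much of the training is supervised.

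**1. Which app is meant?** WeChat and Tencent Meeting are also smartphone apps, so the aim taken by itself could cover them. The Introduction closes off that reading by naming Care-PD and saying *solely*. Adherence Promotion also treats the video conference as something separate, because log-in time is recorded for the conference and for Care-PD respectively.

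**2. The three processes in the aim**

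| Process | Inside Care-PD | Also relied on |
|---|---|---|
| Recruitment and screening | Sign-up, record upload, ADL form, consent, Research and Recruitment module | WeChat; community and hospital advertising; staff help with installation and registration; neurologist video evaluation |
| Exercise | Tai Chi and stretching videos, reminders | Video conference with camera on, supervised live and recorded; WeChat and Tencent Meeting for communication |
| Outcome evaluation | All eight questionnaires | Caregiver help where needed, which is not another channel |

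Reminders are not counted against the claim, because the Intervention section says Care-PD sends them. The third process is app-based as stated. The first two are not.

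**3. Does any arm isolate the app for training?** The Intervention section applies supervision to the exercise intervention as a whole, and Adherence Promotion does so without naming an arm. The Stretching Exercises Group section names no supervisor of its own but makes no exception either. The Control Group section withholds the exercise videos until after the trial. So exercise is either supervised live or absent.

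**4. How much training is affected?** Inputs: three sessions a week for 12 weeks (Intervention); 180 participants allocated 1:1:1 (Participants).

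- Sessions per participant: 3 × 12 = 36
- Participants in the two exercise arms: 2 × (180 / 3) = 120
- Planned person-sessions: 36 × 120 = 4,320
- Of these, planned as app without live supervision: 0

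The 4,320 is a ceiling. The drop-off of 30–35% allowed for in Sample Size would lower it but would leave the last line at zero.

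**5. What can still be learned?** Recruitment, retention, attendance and log-in time describe how well the whole package worked. They cannot divide the credit between the app and the people and channels around it.

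**The case against.** The strongest reply is that this is loose wording. Advertising and WeChat are how people hear of the study, while enrolment itself runs through Care-PD. Outcome evaluation is in the app. The control arm, 60 of 180, uses the app without coached sessions, so its retention and questionnaire completion are seen without them. The live supervision is described openly, the abstract presents the study as one of efficacy, and the primary outcomes are M-EDL and PDQ-39. The feasibility data are collected, and their analysis may be set out in a fuller document.

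Much of this stands, and it limits the point. A reader might infer that the trial cannot address its first aim at all. The documents do not support that: formal enrolment and outcome evaluation can be described as app-based. What the reply does not remove is the gap in outreach and screening and in training. The control arm cannot fill it, since it does no app-based exercise and goes through the same assisted registration and video screening. Nor does the point rest on what a condensed article leaves out; it rests on two things the article states that do not agree.

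A reader might also take exclusion criterion 5, "Inability to use a smartphone or lack of assistance from family members or caregivers to do so", to mean that everyone who does not use a smartphone is shut out, and that this contradicts the aim. The wording is ambiguous: it may remove only people who can neither use a phone nor get help. The protocol provides for researcher guidance and caregiver help, and needing access to a phone is inherent in an app trial. The criterion limits generalisability, and the Discussion already acknowledges difficulty with phones as a limitation. The protocol gives no figure for how many people the criterion would remove, so no corrected feasibility percentage can be derived.

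**Conclusion.** The point holds in a limited form. Two of the three processes named in the aim, recruitment with screening and exercise training, depend on channels and staff outside Care-PD. The third, outcome evaluation, does not. All exercise, up to 4,320 planned person-sessions, is to be supervised live. The trial can support a statement about the practicability of the package as delivered, but not an app-only statement for recruitment, screening or training.

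This assumes that the general statement on supervision covers every session in both exercise arms, which is how the Intervention section reads. The conclusion does not depend on which video platform is used, on how exclusion criterion 5 is read, or on any rate of exclusion or retention. Randomisation, sample size and the comparison of arms on the primary outcomes are untouched. What changes is what the trial may conclude about its first aim.

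**What to change.** 1. In the aim, in the other Introduction statements and in the Discussion, replace *only*, *solely* and *entirely* with a description such as: an app-centred remote programme with live video supervision and staff-assisted recruitment. Limit the practicability conclusion to that package.
2. Name recruitment, retention, attendance and log-in time, all already collected under Adherence Promotion, together with questionnaire completion, as the outcomes for this aim.
3. Report descriptively how many people were screened out under exclusion criterion 5, as a limit on generalisability. They need not be scored as failures of practicability, since that would be a choice of definition and not a correction.

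The cost is rewording and a count of exclusions by reason. Allocation, sample size, sessions and visit schedule stay as they are. The real loss is the app-only claim and the claim to be the first trial in China run entirely by app.
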